### Cost-effectiveness

A cost effectiveness module will be conducted in order to assess the incremental cost-effectiveness of screening and treatment of the household members of SMC-Children. To undertake cost effectiveness analysis, it is important that data on both costs and effectiveness are linked in such a way that only the incremental costs of those resources that produce the incremental effects are measured. The financial and economic costs (from the provider perspective) and cost-effectiveness of each intervention will be determined in order to better inform decision making. In addition, cost savings to the health systems due to malaria cases averted will be estimated. This cost effectiveness component will be carried out into two phases. In the first phase, the protocol and other study materials development will be guided by information collected via a literature review. In the second phase, the developed study materials will be used to collect the intended information by performing field interviews and observations.

Applying a micro-costing approach, information will be collected regarding the resources and costs associated with routine SMC and the new intervention. Screening and treatment of the household members of SMC-Children will be an “add-on” to existing SMC program. Costs for the introduction of the Screening and treatment of the household members of SMC-Children will be estimated for the two years of the intervention. The introduction costs refer to those investments that occur during the initial years of the introduction and typically include investments in additional training if needed, planning activities for a new intervention, sensitization etc. A cost calculation framework will be prepared in Excel, in which outputs will be generated (micro-costing) by multiplying p (unit cost of each item) with q (quantity of each item).

### Outcomes

The primary outcome is the incidence of clinical malaria evaluated within each year of the study in primary study participants i.e. children under SMC coverage. Secondary outcomes include (i) RDT and microscopy positivity rate from the beginning to the end of the follow-up, (ii) tolerance and safety i.e. the risk of adverse events (AEs) and serious adverse events (SAEs) after SMC drug uptake (AQSP) and after treatment with DHA-PPQ for household members (iii) prevalence of mutant alleles of *pfcrt*, *pfmdr1*, *pfdhfr*, and *pfdhps*, *plasmepsin*, and *K13* in malaria positive samples from the enrolment to the end of the follow-up periods, and (iv) adherence, (v) cost-effectiveness, and (vi) acceptability of the intervention which will be assessed qualitatively.

### Statistical analysis

The primary analysis will be a comparison of incidence rates between intervention and control treatment arms; incidence rate ratios and 95% confidence intervals will be also provided. Pooled incidence rate ratio and 95% CI will be calculated (if no interaction with time observed) using Poisson regression, adjusted for the year of study. The incidence of reported adverse events and serious adverse events will be summarized as a proportion of participants experiencing any of the events and a specific type of the event (defined by MEDRA) from the initiation of the treatment to day 30 after the last dose of the treatment. The AE incidence will be compared between study arms using Poisson regression. Prevalence of mutant alleles will be calculated as a proportion of samples with mutation for each study year and temporal trend will be explored using logistic regression and actual time of sample collection. Any comparisons between study arms including all participants will adjust for household clustering. A detailed statistical analysis plan will be produced before the database lock. Database will be locked at the final monitoring visit.

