### Sample size calculation

The aim of this study is to demonstrate that SMC for children between aged 3–59 months associated with the screening household members (through standard HRP2 RDT) and treatment if proven positive is superior to SMC alone in reducing the incidence of clinical malaria after 1 year. In this superiority trial the sample size is calculated to attain sufficient power to determine independently the relevant difference in malaria incidence rate between the control and the intervention arms, using classic RDT. The sample size estimation is performed under the assumption that the average number of malaria episodes per child aged between 3 and 59 months per year since the implementation of SMC in Nanoro health district varied between 1.38 and 1.76 [17–19]. Sample size of 236 in each arm will give at least 80% power to detect a 20% decrease in incidence of malaria after 1 year in comparison to a baseline incidence rate in the control arm (SMC) between 1.5–2.0 malaria cases per year, assuming a one-sided test with significance level of 0.025 and large samples z-test of the Poisson event rate difference (PASS software). To account for 10% study drop-out rate for any reason, the sample size will increase to 263 in each arm. Therefore, the final estimated sample size for this study is 526 households, with at least one child aged between 3 and 35 months to allow a follow up of the children during the study period and while benefiting of SMC. One child from each household (primary participants) will be included in the primary analysis, assuming that each household will have an average of 2 children under SMC coverage, about 1052 children under SMC coverage are expected [11]. The expected number of household members is estimated at about 1315 (263 × 5) under the assumption that each household from the intervention arm will have an average of 5 members. Data will be analysed with R software using the appropriate tests depending on the variables. Adherence to treatment and acceptability of the strategy (focus group discussion) will be assessed qualitatively.

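### The pooled Poisson model and the Poisson-based sample size make no allowance for children differing in malaria risk or for the same child supplying two years of data

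*Protocol article*

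**What the plan says.** **Sample size calculation.** "Sample size of 236 in each arm will give at least 80% power" to "detect a 20% decrease in incidence of malaria after 1 year", for a "baseline incidence rate in the control arm (SMC) between 1.5–2.0 malaria cases per year". The test is one-sided at 0.025, a "large samples z-test of the Poisson event rate difference". A 10% drop-out allowance raises the number to 263 per arm. Earlier local incidence "varied between 1.38 and 1.76" episodes per child-year; only these means are given, with no standard deviation or dispersion. The primary analysis takes one child per household.

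**Data collection.** The same children are followed for 24 months. Superiority is judged over one season, the analysis is repeated in year 2, and the two years are then pooled.

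**Statistical analysis.** The primary analysis is described only as a comparison of incidence rates, with rate ratios and 95% confidence intervals. The pooled ratio, calculated if there is no interaction with time, is obtained "using Poisson regression, adjusted for the year of study". The one rule on dependence reads: "Any comparisons between study arms including all participants will adjust for household clustering". A detailed analysis plan is to follow before database lock.

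**The concern.** A Poisson model with its own model-based variance assumes that every child in an arm has the same underlying rate. The trial's rationale says otherwise. The Background argues that infected parents and older siblings in some households keep reinfecting the children, and cites uneven net use (44.1% slept under a net the night before the survey). Under that premise, children's rates differ and counts vary more than Poisson allows. Much of the difference would plausibly persist into the second season, so a child's two yearly counts would be correlated.

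The plan has a rule for correlation, but it is written for comparisons of all participants. It does not reach the analysis of one child per household, where the dependence lies between two years of the same child.

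Two things are at stake. Confidence intervals for the rate ratios could be too narrow, the pooled one most of all. And the stated 80% power has no room for the variance that a valid analysis would use.

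**Working it through.** **Inputs from Sample size calculation:** 236 per arm, 80% power, one-sided 0.025, control rate L1 = 1.5 to 2.0 per year, rate ratio 0.8, 10% drop-out. That section puts 526 households in the whole trial, while the abstract puts 526 in each arm; the section's figure is used here.

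**Assumed, because the documents are silent:** each child's rate is multiplied by a gamma variable with mean 1 and variance k, with k from 0 to 1.0. For the pooled analysis the multiplier is the same in both years.

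**1. Reproduce the plan's figure.** With L1 = 1.5 and L2 = 1.2:

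n = (z0.975 + z0.80)² (L1 + L2)/(L1 − L2)² = 7.849 × 2.7/0.09 = 235.5, so 236. Then 236/0.9 = 262.2, so 263.

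Power at 236 is 80.1% at 1.5 per year and 90.0% at 2.0. The figure reproduces exactly with variance equal to mean, so it contains no allowance for overdispersion.

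**2. Error of a Poisson test with model-based variance.** Under the null, Var(Y) = L + kL². The true variance exceeds the Poisson variance by a factor of φ1 = 1 + kL for one year, and φ2 = 1 + 2kL for two pooled years with a shared multiplier. The true one-sided error is 1 − Φ(1.96/√φ). For example, at k = 0.5 and L = 1.5: φ1 = 1.75, 1.96/1.323 = 1.482, error 6.92%; φ2 = 2.50, 1.96/1.581 = 1.240, error 10.76%.

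| k (L = 1.5) | φ1 | One year | φ2 | Pooled |
|---|---|---|---|---|
| 0 | 1.00 | 2.50% | 1.00 | 2.50% |
| 0.1 | 1.15 | 3.38% | 1.30 | 4.28% |
| 0.2 | 1.30 | 4.28% | 1.60 | 6.06% |
| 0.5 | 1.75 | 6.92% | 2.50 | 10.76% |
| 1.0 | 2.50 | 10.76% | 4.00 | 16.35% |

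At k = 0.5, coverage of a nominal 95% interval is 1 − 2 × 0.0692 = 86% for one year and 1 − 2 × 0.1076 = 78% pooled. At L = 2.0, with k from 0.1 to 1.0, the error is 3.7% to 12.9% for one year and 4.9% to 19.0% pooled.

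**3. Simulation check.** 20,000 gamma-Poisson trials per setting, 236 per arm, L = 1.5, Wald test on the log rate ratio. One-sided error for one year and pooled: k = 0, 2.4% and 2.6%; k = 0.2, 4.1% and 6.0%; k = 0.5, 6.8% and 10.8%; k = 1.0, 10.1% and 16.1%. These agree with the formula.

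**4. Power of the one-year test with the variance corrected.** v = L1 + kL1² + L2 + kL2² = 2.7 + 3.69k. Power = Φ(0.3/√(v/236) − 1.96). For 80% power, n = 7.849 v/0.09.

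| k (L1 = 1.5) | v | Power at 236 | n per arm for 80% | After 10% drop-out |
|---|---|---|---|---|
| 0.1 | 3.069 | 74.9% | 268 | 298 |
| 0.2 | 3.438 | 70.0% | 300 | 334 |
| 0.5 | 4.545 | 58.0% | 397 | 442 |
| 1.0 | 6.390 | 44.6% | 558 | 620 |

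At L1 = 2.0, power is 84.6%, 79.2% and 64.9% for k = 0.1, 0.2 and 0.5.

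**5. Would negative binomial regression alone be enough?** For a single year, yes. With two child-year records treated as independent it captures φ1 but not the covariance between years, so the variance is still short by φ2/φ1. At k = 0.5 this is 2.50/1.75 = 1.43, and the one-sided error is 1 − Φ(1.96/1.195) = 5.1%, about twice nominal.

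**The case against.** The strongest reply is that the article names a model and not a variance estimator. Poisson regression is compatible with scaled or robust standard errors, and a later analysis plan may specify them. That stands: the use of model-based variance is an inference. It does not clear the plan, because the article itself sets a dependence rule and draws it so that it misses the pooled analysis of one child per household. The sample size, moreover, is already fixed on variance equal to mean.

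A reader might go further and infer that, because each child contributes two years, the trial's one-sided 2.5% error rate is exceeded. The documents do not support that reading, for three reasons.

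- The 0.025 belongs to the superiority test over one season, in which repeated years play no part. The Poisson variance of that test is known only from the sample size section. The pooled analysis has a 95% interval and no stated test level.
- Any excess depends on a dispersion that the documents do not give. At k = 0 there is none, even with two years per child.
- The pooled figures assume that a child's relative risk is identical in both seasons. If it is only partly shared, the pooled error is lower.

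**Conclusion.** The concern holds in conditional form. As written, the plan provides neither for differences in risk between children nor for two years of data from one child. If children differ in risk and the model-based variance is used, intervals are too narrow. At 1.5 episodes per year and an assumed k of 0.1 to 1.0, one-sided error would be 3.4% to 10.8% for a one-year Poisson test and 4.3% to about 16% for the pooled analysis with fully shared risk, against a nominal 2.5%.

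The sample size consequence is firmer, because it does not depend on which standard error is eventually chosen. The 236 per arm reaches 80% at 1.5 episodes per year only if there is no overdispersion at all. That children differ is implied by the trial's rationale; by how much is not stated, so these sizes are a range and not an estimate.

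**What to change.** **Statistical analysis.** For the year-1, year-2 and pooled analyses, specify Poisson regression with a log person-time offset and robust (sandwich) standard errors clustered on household. With one child per household this is the same as clustering on the child, so it also covers the child's two years; it brings the error back to about nominal. Negative binomial regression is an acceptable alternative for the single-year analyses, but in the pooled analysis it too needs clustering on child or household.

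**Sample size calculation.** State an assumed dispersion, with its source, and restate the power at 236 per arm, for example as the range in step 4.

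**Cost.** No new data are needed and the methods are standard in R, the software already named. The price is wider intervals and a less favourable stated power, which at 1.5 episodes per year falls below 80% for any k above about zero. The wording should be settled before database lock.

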### Oversight and monitoring

Internal monitoring system by the NMCP is planned. This internal monitoring will be conducted to check for data collection accuracy and completeness of adverse events, and to verify the enrolment procedures by field workers. In addition, the project will be adequately monitored following a proposed monitoring plan. This will be led by an external experienced monitor hired from reference research center across the Greater Sahel research institutes. The monitor will verify the best conduct of the study through site visits and periodic phone calls with the principal investigator and other study staff. The monitor will have access to the study database that he/she will progressively review for consistency against source documents. At least four monitoring visits are planned.

Besides the monitoring and internal evaluation, an external intermediate scientific review will be performed. A scientific reviewing committee (SRC) will be set up before the study start. The members of the SRC will be selected from the Academy of Sciences of Burkina Faso, the Malaria task force of Burkina Faso and among international famous senior malariologists with strong experience in SMC intervention. The SRC will play the role of project monitoring group and will provide an external overview of all aspects of the study.

### Dissemination

Dissemination is critical for the adoption and translation of evidence-supported interventions into policy. Therefore, our consortium considers the dissemination component as an integral part of this study in order to ensure that our research findings will have the expected public health impact. This is particularly important in resource limiting settings where there are usually significant gaps or delays between the production of scientific evidences and their translation into policy. Taking this into account, the dissemination of the study results is planned not only through regular reports (implementation, progress, final), scientific papers and conference attendance, but also through meetings with various audiences of interest, including key stakeholders such as decision-makers and public health authorities; health workers; and members of the communities (including study participants and local community) directly impacted by the study results.

## Discussion

In Sahel countries, with high seasonal malaria transmission, SMC is an important strategy for reducing malaria burden. Despite the implementation of SMC intervention as a complement to multiple other malaria control measures, such as mass distribution of LLIN, malaria burden remains high in the most vulnerable groups including children younger than five years suggesting that the expected impact of this promising intervention is not reached. In order to achieve global malaria target by horizon 2030, development of innovative strategies to improve the efficacy of these existing malaria control measure is essential. This study aims to assess the impact of an improved SMC strategy adding roommates malaria screening and treatment with DHA-PPQ if positive. If confirmed to be beneficial, this strategy will contribute to breaking the cycle of continuous infection of children from parents and older siblings, as household members are not yet targeted by any specific intervention.

The choice for DHA-PPQ is driven by several reasons including its adoption as first line treatment for uncomplicated malaria in Burkina Faso [2, 21], its longer post-treatment prophylactic effect and most importantly its proven efficacy and safety in the area [22, 23].

Microscopy will be used in addition to RDT for the detection of malaria cases and asymptomatic parasitaemia in order mitigate the issue of false positive RDT due to the persistence of HRP2 antigen after a successful malaria treatment. Furthermore, microscopy will allow a better characterization of the detected cases in terms of parasitaemia, parasite species as well as gametocyte carriage which is critical for the transmission in the area.

SMC is delivered as a prevention measure during each malaria season but in this study the follow-up period is extended up to 24 months in order to cover two consecutive malaria seasons. The rationale for this extension include increasing the power to detect rare study outcomes such as severe malaria, related-mortality, rare safety signals with special interest to known severe reactions to SMC drugs and to DHAPPQ and to have an overview of the impact of the intervention overtime.

Superiority of the SMC + roommates malaria screening and treatment intervention over the routine implementation of SMC alone is expected. Therefore, the study will greatly contribute to identifying measures to reduce the malaria burden in Burkina Faso. By reducing morbidity and mortality, this study will have significant economic impact by promoting economic development and welfare in Burkina Faso, as malaria constitute an important threat to the development in the country.

We anticipate that holding SMC campaigns during the COVID-19 pandemic, combined with the fact that some parts of the country are prone to insecurity, may be challenging. However, it is important to stress that the 2020 SMC campaign has been fully implemented in the study area without any disturbance related to COVID-19 and/or security issue. In addition, the study area, Nanoro is located at 85 km from Ouagadougou, the capital city in the Central West Region of Burkina Faso, where we have not experienced any particular security issues so far.

Close monitoring of *P. falciparum* resistance markers to antimalarial drugs [24–27] will be conducted because the sustainability of any intervention, especially wide scale community-based intervention such as SMC, relies on the optimal efficacy of the drugs, especially as SMC induces a substantial drug pressure. Hence a close monitoring of the selection of resistance markers in the parasite population is paramount to describe the impact of the strategy.

Finally, this is a multidisciplinary collaborative research involving key stakeholders such as the WorldWide Antimalarial Resistance Network (WWARN), part of the Infectious Disease Data Observatory (IDDO) and policy makers such as the National Malaria Control Program (NMCP). The involvement of the NMCP will facilitate the rapid translation of the studyfindings into policy. In case of promising results, the NMCP will endorse the leadership of advocating with its financial and technical partners on the need to change the policy with the adoption and extension of this new strategy at national level. To better achieve this goal, a large-scale dissemination workshop will be organized by the NMCP to share the project findings. This workshop will bring together all key stakeholders of malaria policy decision making in Burkina Faso involving for example WHO, UNICEF, USAID, WAHO. The study could also be scaled up easily at regional level (through the regional Roll Back Malaria network) especially in other Sahelian countries with similar malaria epidemiological profile and where SMC is also implemented.

## Conclusion

This study will respond to a major public health concern by providing evidence of the efficacy of an innovative strategy to boost the impact of SMC intervention. This new approach should necessarily complement the existing ones to achieve the optimal impact in malaria control and elimination.

## Data Availability

Data supporting the conclusions of this article are included within the article and its additional files.

## Abbreviations

ACT: Artemisinin-based Combination Therapies
AE: Adverse Event
AQSP: Amodiaquine- Sulfadoxine-Pyrimethamine
CRUN: Clinicla Research Unit of Nanoro
DHAPPQ: Dihydroartemisinin-Piperaquine
DNA: Deoxyribonucleic acid
HDSS: Health and Demographic Surveillance System
HRP2: Histidin Rich Protein 2
IPTp: Intermittent Preventive Treatment in pregnancy
K13: Kelch 13
LLIN: Long-Lasting Insecticide treated Nets
NHD: Nanoro Health District
NMCP: National Malaria Control Program
PCR: polymerase chain reaction
Pf: *Plasmodium falciparum*
Pfcrt: *Plasmodium falciparum* chloroquine resistance transporter gene
Pfdhfr: *Plasmodium falciparum* dihydrofolate reductase
Pfdhps: *Plasmodium falciparum* Dihydropteroate synthetase
Pfmdr1: *Plasmodium falciparum* Multidrug resistance gene
RDT: Rapid Diagnostic Test
RST: Roommates Screening and Treatment
SAE: Serious Adverse Event
SMC: Seasonal malaria chemoprevention
SNP: Single Nucleotide Polymorphism
WWARN: WorldWide Antimalarial Resistance Network.
